## Abstract

**Introduction:**

Using pre-procedure analgesia with the risk of apnoea may complicate the Less Invasive Surfactant Administration (LISA) procedure or reduce the effect of LISA.

**Methods:**

The NONA-LISA trial (ClinicalTrials.gov, NCT05609877) is a multicentre, blinded, randomised controlled trial aiming at including 324 infants born before 30 gestational weeks, meeting the criteria for surfactant treatment by LISA. Infants will be randomised to LISA after administration of fentanyl 0.5–1 mcg/kg intravenously (fentanyl group) or isotonic saline solution intravenously (saline group). All infants will receive standardised non-pharmacological comfort care before and during the LISA procedure. Additional analgesics will be provided at the clinician’s discretion. The primary outcome is the need for invasive ventilation, meaning mechanical or manual ventilation via an endotracheal tube, for at least 30 min (cumulated) within 24 h of the procedure. Secondary outcomes include the modified COMFORTneo score during the procedure, bronchopulmonary dysplasia at 36 weeks, and mortality at 36 weeks.

**Discussion:**

The NONA-LISA trial has the potential to provide evidence for a standardised approach to relief from discomfort in preterm infants during LISA and to reduce invasive ventilation. The results may affect future clinical practice.

**Impact:**

Pre-procedure analgesia is associated with apnoea and may complicate procedures that rely on regular spontaneous breathing, such as Less Invasive Surfactant Administration (LISA).This randomised controlled trial addresses the effect of analgesic premedication in LISA by comparing fentanyl with a placebo (isotonic saline) in infants undergoing the LISA procedure. All infants will receive standardised non-pharmacological comfort.The NONA-LISA trial has the potential to provide evidence for a standardised approach to relief from discomfort or pain in preterm infants during LISA and to reduce invasive ventilation. The results may affect future clinical practice regarding analgesic treatment associated with the LISA procedure.

## Introduction

Respiratory distress syndrome (RDS) caused by surfactant deficiency remains a significant reason for neonatal mortality and short- and long-term morbidity in preterm infants.^1^ RDS usually develops during the first 24 h of the delivery, and most infants with RDS present with breathing difficulties and an increased need for oxygen supplementation within the first few hours of birth. Surfactant decreases alveolar surface tension and helps to keep the lungs aerated, allowing pulmonary gas exchange. Exogenous surfactant treatment of preterm infants with RDS reduces mortality and long-term morbidity.^2–4^

Less Invasive Surfactant Administration (LISA) is a strategy to administer surfactant to infants with worsening RDS despite optimised non-invasive ventilation. LISA aims to prevent alveolar collapse and avoid endotracheal intubation and invasive ventilation before, during, and after surfactant administration.^4–6^ LISA involves surfactant administration via a thin catheter placed in the trachea using laryngoscopy on a spontaneously breathing infant. Before LISA was introduced, surfactant was administered via an endotracheal tube followed by invasive ventilation and later via the INtubation-SURfactant-Extubation (INSURE) method with immediate extubation following surfactant administration. Studies have shown that using LISA reduces the incidence of intraventricular haemorrhage (IVH), mortality, the need for invasive ventilation, and the risk of bronchopulmonary dysplasia (BPD) in preterm infants.^7,8^ LISA is currently considered the preferred method of surfactant administration in spontaneously breathing infants according to the European Consensus Guidelines on Management of RDS,^4^ and LISA is increasingly used in NICUs worldwide.^9^

However, the need for analgesic premedication in LISA is debated. In a recent study of 153 LISA experts,^10^ 41% indicated no use of pre-procedure sedatives or analgesics, and 49% reported using fentanyl as a pre-procedure treatment. On the contrary, 4% indicated no use of non-pharmacological treatment. There is a delicate balance between the desired effect of analgesia reducing discomfort and pain associated with laryngoscopy as opposed to acute cardiovascular side effects and the risk of over-sedation and apnoea. This may potentially impede the procedure and result in the need for positive pressure ventilation, which may harm the surfactant-deficient lung.^11,12^ Observational data suggests the ease of performing LISA to be unaffected by whether opiates are used or not.^13^

The NONA-LISA trial (ClinicalTrials.gov, NCT05609877) compares LISA with saline to LISA with 0.5–1 mcg/kg fentanyl in infants born before 30 gestational weeks and evaluate the need for invasive ventilation via an endotracheal tube for at least 30 min (cumulated) within 24 h of the procedure. Secondary outcomes include the number of laryngoscopy attempts, duration of the procedure, modified COMFORTneo score during the procedure, bronchopulmonary dysplasia at 36 weeks, and mortality at 36 weeks.

## Methods

### Design and setting

The NONA-LISA trial is a multicentre, blinded, randomised controlled trial of fentanyl 0.5–1 mcg/kg or placebo (isotonic saline), administered to infants born before 30 gestational weeks who meet the criteria for surfactant treatment by LISA. A total of 324 infants will be randomised in a 1:1 ratio to one of the two arms. They will be followed up at 36 weeks PMA and at hospital discharge (shown in Fig. 1). The trial protocol conforms with the Standard Protocol Items: Recommendations for Interventional Trials (SPIRIT),^14^ and the trial results will be reported in compliance with the Consolidated Standards of Reporting Trials (CONSORT) Statement.^15^ The trial will be initiated at (but not limited to) the Danish level III Neonatal Intensive Care Units (NICUs).

**Fig. 1 Fig1:**
[figure not shown]
The Consolidated Standards of Reporting Trials (CONSORT) diagram of the NONA-LISA trial. Abbreviations: NONA-LISA NON-pharmacologic Approach Less Invasive Surfactant Administration, LISA Less Invasive Surfactant Administration, GA gestational age.

### Population

Infants will be eligible for inclusion if they are born before 30 gestational weeks at one of the trial sites and meet the criteria for first-choice surfactant treatment by LISA as described by Sweet et al.^4^: worsening babies with RDS and FiO_2_ > 0.30 on CPAP pressure ≥6 cm H_2_O. The primary respiratory support is CPAP in all four units.

Infants will be excluded if they meet any of the exclusion criteria; 1) suspicion of lung hypoplasia, 2) endotracheal intubation at any time before randomisation, 3) suspicion of pneumothorax, pulmonary haemorrhage or pleural effusion before LISA, 4) major congenital anatomical anomalies as described by the European Surveillance of Congenital Anomalies (EUROCAT).^16^

### Randomisation

Participants will be randomly assigned to the saline or fentanyl group in a 1:1 ratio using computer-generated random allocation sequences with permuted blocks of varying sizes (two and four). The randomisation sequence will be stratified by trial site and gestational age at birth (more or less than 28 completed gestational weeks). Once randomised in the Research Electronic Data Capture (REDCap) system, all entry data will automatically be transferred to the electronic case record forms (eCRF) linked to the infant’s unique identification number. The allocation sequence is pre-coded and generated from the randomisation programme. A person not involved in the trial will generate the allocation sequence. The clinical staff will enrol participants.

### Blinding

Blinding will be secured by the following means: The patient will be randomised after entering stratification variables in REDCAP. The randomisation sequence will be generated by one person unrelated to the study. The trial medication (fentanyl or isotonic saline) will be prepared once per day in sealed syringes with similar appearance and weight by the pharmacy or staff not involved in patient care. Thus, neither staff involved in screening or treatment of patients nor the parents will know the treatment allocation. Primary analyses will be performed blinded to the group allocation (Group A compared with Group B) and presented to all authors, who will agree on two alternative written interpretations before the randomisation code is unblinded to reduce the risk of interpretation bias.

### Interventions

Participants are randomised to receive LISA with fentanyl 0.5-1 mcg/kg (fentanyl group) or LISA with isotonic saline (saline group). All infants will receive standardised non-pharmacological comfort care before and during the LISA procedure (Online Supplement, Appendix A). All LISA procedures will be performed using video laryngoscopes according to the Hobart method.^2,3^ Both groups will receive the neonatal unit’s standard pre-procedure care (e.g., atropine and caffeine), which will not be standardised across trial sites. Naloxone may be administered at the clinician’s discretion and will not be used routinely. In both groups, the infant’s level of discomfort or pain will be monitored continuously during the procedure by vital signs and a modified COMFORTneo score (Online Supplement, Appendix A).^17^ Open-label analgesics can be administered to all participants at the clinician’s discretion by indications of non-tolerance (e.g., modified COMFORTneo score >14).

All administered medications will be registered. A single dose of 200 mg/kg porcine surfactant (Curosurf®, Chiesi Pharma AB, Italy) will be used in this trial.

### Outcomes

#### Primary outcomes

The primary outcome of this trial is the need for invasive ventilation, meaning mechanical or manual ventilation via an endotracheal tube for at least 30 min (cumulated) within 24 h of the procedure. Non-invasive ventilation (NIV) is not included in the primary outcome.

#### Secondary outcomes

The secondary outcomes include:Unique and composite outcome of death or moderate/severe BPD^18^ at 36 weeks PMA.Adverse events during the procedure (from the introduction of the laryngoscope blade into the oral cavity to the removal of the catheter) in terms of apnoea that require bag and mask ventilation, desaturation with an absolute decrease in peripheral oxygen saturation >20% from pre-procedure baseline, and bradycardia <100 BPM individual outcomes.^19^Pain or discomfort during the procedure (according to modified COMFORTneo score >14^17,20,21^).Highest modified COMFORTneo score during the procedure.Need for a second dose of surfactant.Incidence of LISA procedures resulting in the INSURE procedure.Incidence of observed surfactant reflux.Incidence of observed injury to the upper airway.Incidence of observed injury to the lower airway.Incidence of invasive ventilation within 48 h after LISA.Cumulated duration of invasive ventilation during hospitalisation.Cumulated duration of any non-invasive respiratory support during hospitalisation.Cumulated duration of any respiratory support during hospitalisation.Procedural duration from the introduction of the laryngoscope blade over the lips to the removal of the catheter.Number of attempts to visualise vocal cords (laryngoscopy) where the laryngoscope is completely removed from the oral cavity between attempts.Incidence of pneumothorax within 48 h after LISA.Incidence of massive pulmonary haemorrhage within 48 h after LISA (aspiration of haemorrhagic secretions from the trachea concurrent with the need for escalated respiratory support).^22^Duration of hospitalisation.Morbidities in terms of necrotising enterocolitis (according to the radiographic signs of Bell’s Staging Criteria),^23^ treatment-demanding retinopathy of prematurity, intraventricular haemorrhage grade 3–4 and periventricular leukomalacia (according to the Papile classification)^24^ as individual outcomes.

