#### Data collection

Baseline characteristics will include infant gestational age at birth, delivery mode, singleton or multiple births, birth weight, sex, APGAR score (1, 5, and 10 min after delivery), resuscitation measures during the first 30 min after birth, first blood gas, umbilical arterial and venous pH, standard base excess, and lactate. Information on vital signs (oxygen saturation, FiO_2_, and heart rate) will be collected 15 min before and after the procedure. Information on treatment with antibiotics, fluids, vasopressors, and early caffeine before the LISA procedure will be recorded. We will calculate the time from meeting the criteria for surfactant treatment until the procedure starts. We will also include maternal information regarding smoking status, diseases (diabetes mellitus, amnionitis as per the obstetrician, preeclampsia, and eclampsia), and antenatal administration of steroids, magnesium sulphate, indomethacin, and antibiotics, including timing.

A generic procedure description will be created for the clinician to use in the medical records to ensure that all information, including modified COMFORTneo score before the procedure, administration of atropine, early caffeine and naloxone, and indications for additional fentanyl administration and cumulated dosage, is recorded uniformly.

If the infant is discharged to a step-down unit, information will be retrieved from that unit.

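### The procedural adverse-event outcome counts apnoea, desaturation and bradycardia only from blade insertion to catheter removal, although the randomised drug is given earlier

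*Protocol article*

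**What the plan says.** The secondary outcomes list adverse events confined to the interval "Adverse events during the procedure (from the introduction of the laryngoscope blade into the oral cavity to the removal of the catheter". The events are defined "in terms of apnoea that require bag and mask ventilation, desaturation with an absolute decrease in peripheral oxygen saturation >20% from pre-procedure baseline", together with a heart rate below 100 BPM, each as an individual outcome.

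The study drug comes first. The abstract (Methods) states: "Infants will be randomised to LISA after administration of fentanyl 0.5–1 mcg/kg intravenously (fentanyl group) or isotonic saline solution intravenously (saline group". The Impact section gives the reason for the trial: "Pre-procedure analgesia is associated with apnoea and may complicate procedures that rely on regular spontaneous breathing". The Introduction and the Discussion repeat that concern.

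Outside the window, the Data collection section provides for this: "Information on vital signs (oxygen saturation, FiO_2_, and heart rate) will be collected 15 min before and after the procedure". It names neither apnoea nor bag-and-mask ventilation for those periods, and no listed outcome is defined on those readings. The primary outcome is invasive ventilation through an endotracheal tube "for at least 30 min (cumulated) within 24 h of the procedure", and non-invasive ventilation does not count towards it.

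**The concern.** Both arms undergo the same laryngoscopy, catheterisation and comfort care. The planned difference between them is an intravenous opioid or saline given beforehand. A window from blade to catheter suits harms of the instrumentation, which the arms share. It suits harms of the drug less well, because it opens some time after the injection and closes when the catheter comes out, whether or not the drug is still acting.

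At stake is how a null result would be read. If the trial reported similar rates of apnoea needing bag-and-mask ventilation, readers could take this as reassurance about opioid premedication, although part of the period at risk was never counted. The reference value for desaturation adds to the problem. It is called a pre-procedure baseline without saying whether it precedes the injection. If it were read after the drug, a fall already under way would be absorbed into the baseline.

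**Working it through.** **Step 1. What is counted, and when.** Set the order of events in the article against the outcome definitions.

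| Period | Apnoea with bag-and-mask ventilation | Desaturation, bradycardia |
|---|---|---|
| Study-drug injection to blade insertion | no outcome | no outcome; vital signs may be collected |
| Blade insertion to catheter removal | counted | counted |
| After catheter removal | no outcome | no outcome; vital signs collected at or over 15 min |

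The window ends at catheter removal, not at blade withdrawal. Events after the blade is out but with the catheter still in place are counted.

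**Step 2. Does another listed outcome fill the gaps?** Only through consequences. The primary outcome needs at least 30 min of endotracheal ventilation. Conversion to INSURE, invasive ventilation within 48 h and the durations of respiratory support record later management. An apnoea that is resolved by mask outside the window appears in none of them as an event.

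**Step 3. Check the formula on the plan's own figure.** Inputs from the sample size section: 45% and 30%, alpha 0.05, power 0.8, total 324 at 1:1. The statistical methods section makes tests two-sided. With pooled variance under the null and no continuity correction:

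n per arm = [1.96·√(2·0.375·0.625) + 0.8416·√(0.45·0.55 + 0.30·0.70)]² / 0.15² = 162.3, rounded up to 163, so 326 in total. This is within 1% of 324. At 162 per arm the power is 0.799. The plan's figure reproduces, and nothing in this point changes it.

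**Step 4. How much could the window matter?** The article gives no rates for these events and no interval between injection and blade, so the inputs here are assumptions. Let s be the saline rate, f the fentanyl rate if all drug-caused events were counted, and x the share of the excess (f − s) that falls outside the window. For simplicity all saline events are placed inside the window. The recorded fentanyl rate is

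r = s + (f − s)(1 − x),

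and with n = 162 per arm and p̄ = (s + r)/2,

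power = Φ{ [ (r − s)√n − 1.96·√(2p̄(1 − p̄)) ] / √( s(1 − s) + r(1 − r) ) }.

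Worked case with s = 15%, f = 30%, x = 0.5: r = 0.15 + 0.15·0.5 = 22.5%. The numerator is 0.075·√162 − 1.96·0.552 = 0.955 − 1.082 = −0.127. The denominator is 0.549. The ratio is −0.232 and the power is 0.408.

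| Share of excess outside the window | Recorded rates (15% / 30% assumed) | Power | Recorded rates (10% / 25% assumed) | Power |
|---|---|---|---|---|
| 0 | 15% vs 30% | 0.902 | 10% vs 25% | 0.948 |
| 25% | 15% vs 26.25% | 0.708 | 10% vs 21.25% | 0.799 |
| 50% | 15% vs 22.5% | 0.408 | 10% vs 17.5% | 0.500 |
| 75% | 15% vs 18.75% | 0.145 | 10% vs 13.75% | 0.179 |

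The first row matters as much as the last: if none of the excess falls outside, nothing is lost. The table shows sensitivity to x. It does not estimate x.

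**The case against.** The window is the same in both blinded arms, and saline infants who desaturate after catheter removal are missed too. A reader might infer that harm is under-counted in the fentanyl arm alone and that the comparison is therefore biased. The article does not support that. Background events are lost from both arms, and attenuation arises only as far as the drug-caused excess falls outside the window. With no onset times and no drug-to-blade interval, this is a risk and not a demonstrated bias.

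The serious consequences are largely caught by the primary outcome and the other ventilation outcomes, and naloxone use is recorded. The item is openly labelled as covering the procedure, the trial claims no power for it, and the full protocol may contain wider safety reporting. All of this stands and limits the weight of the point. It does not close the gap for mask-managed events, because the window is stated explicitly and is not a detail left open.

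It is also fair to say that nothing shows the baseline to be post-drug. The fault is only that its timing is not fixed.

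Two further inferences are tempting. One is that the primary 24 h clock has no origin for an infant intubated after dosing but before LISA. The wording (24 h of the procedure) need not exclude intubation just beforehand, and handling of such a case is normally left to an analysis plan. The other is that the third exclusion criterion, "suspicion of pneumothorax, pulmonary haemorrhage or pleural effusion before LISA", removes infants after randomisation, whereas the second ends at randomisation. The difference in wording is real, but these are eligibility criteria, no removal of randomised infants is stated, and the primary analysis is by intention to treat. No effect size can be attached to it.

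**Conclusion.** The point holds as a gap in one secondary outcome: should-fix. As written, apnoea needing bag-and-mask ventilation, desaturation and bradycardia are not counted between study-drug injection and blade insertion, or after catheter removal, in either arm, unless they lead to an outcome counted elsewhere. That is a poor match for a trial built on the apnoea risk of premedication. Any attenuation is towards no difference, and its size cannot be derived from the article. The fall in power from 90% to 41%, or from 95% to 50%, rests on assumed event rates, on half of the excess lying outside the window, and on all saline events lying inside it. The timing of the desaturation baseline is a second, smaller ambiguity in the same item. The primary outcome, its sample size and the intention-to-treat analysis are unaffected.

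**What to change.** - Define the three adverse-event outcomes from the start of study-drug injection to a prespecified time after catheter removal. Fifteen minutes is one example, because it matches the vital signs that "will be collected 15 min before and after the procedure". It has no other basis in the article, so the trial team should justify the value it chooses.
- State that the saturation baseline is read before the study drug is given.
- Keep the blade-in to catheter-out count as a prespecified sub-analysis.
- As a minor wording matter, end the third exclusion criterion at randomisation, as the second does.

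**Cost.** The eCRF needs a time stamp for study-drug injection and a field for apnoea with bag-and-mask ventilation outside the procedure. The readings already planned cover only oxygen saturation, FiO2 and heart rate, so they cannot supply the apnoea outcome. If those readings are single values and not continuous, desaturation and bradycardia in the added periods will need to be recorded as events too. The wider count is slightly less comparable with studies that use a procedure-only window, which is why the present count should be kept beside it. The total of 324 does not change.

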#### Sample size estimation and inclusion timeline

The sample size was calculated according to the primary outcome. Previous studies on preterm infants born before 30 gestational weeks report a frequency of invasive ventilation after the LISA procedure from 33%^26^ and 41%^27^ up to 75%.^28^ Based on the incidence of invasive ventilation following LISA, we anticipate that the primary outcome will have an incidence of around 45% in the fentanyl group in our trial. Considering an alpha of 0.05 and a power of 0.8 to detect an anticipated incidence of about 30% for the saline group, this trial will enrol 324 infants in a 1:1 ratio. Based on an article by Wiingreen et al., ~123 infants are born before 30 gestational weeks each year in Denmark with the need for surfactant.^29^ The inclusion will last three to four years, considering an expected inclusion rate of 80%.

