#### Statistical methods

Baseline characteristics will be presented for each group in the trial population. Categorical variables will be presented as frequencies (counts and percentages). Continuous variables will be presented as medians with interquartile ranges [IQR] or as means with standard deviations [SD].

The primary analysis will use the intention-to-treat principle. A secondary analysis will use the per-protocol principle and exclude infants if they receive additional analgesics associated with the procedure.

The primary outcome will be reported as frequencies (counts and percentages) per treatment group with unadjusted absolute risk difference and relative risks with 95% confidence intervals (CI). The number needed to treat for benefit or harm will be reported if the results of the primary analyses show a statistically significant difference between the two exposure groups.

Secondly, a logistic regression model will be performed adjusting for inclusion site and gestational age (<28 weeks vs more than 28 weeks) and the following independent covariates, which are predictors of assisted ventilation and length of ventilation:^30^ repeat doses of prenatal corticosteroids, 5-min APGAR scores, sex, admission illness severity (according to the Score for Neonatal Acute Physiology/SNAP score^31^), oxygenation index, and small-for-gestational-age status.^32^

All secondary dichotomous outcomes will be described and analysed per the same strategy as the primary outcome. At the same time, mean and percentage differences will be calculated for continuous outcomes.

All analyses will be conducted by use of the statistical software R Studio. Two-sided P values less than 0.05 will be considered statistically significant.

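### Hospital stay and respiratory-support durations are compared by mean differences with no provision for death, so a mortality difference between arms would distort them

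*Protocol article*

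**What the plan says.** The Secondary outcomes section of the protocol article lists four durations that accumulate over the admission: "Cumulated duration of invasive ventilation during hospitalisation", "Cumulated duration of any non-invasive respiratory support during hospitalisation", "Cumulated duration of any respiratory support during hospitalisation" and "Duration of hospitalisation". None has a fixed horizon, so each total stops when the admission ends, whether by discharge or by death.

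The Statistical methods section gives one treatment for all such variables: "mean and percentage differences will be calculated for continuous outcomes". It also says "The primary analysis will use the intention-to-treat principle", but has no matching sentence on who enters the comparison of the continuous secondary outcomes.

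Death is an expected event. The secondary outcomes include "Unique and composite outcome of death or moderate/severe BPD" at 36 weeks PMA, so death is counted alone and within a composite. The article does not say how an infant who dies enters any of the four durations.

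**The concern.** A short admission can mean quick recovery or early death, and a mean of raw durations treats the two alike. If one arm loses more infants early, its mean stay and mean support fall for that reason alone.

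The article's own reasoning leaves room for a survival difference. The Introduction credits surfactant and LISA with lower mortality, and the Abstract raises the possibility that premedication weakens the effect of LISA. For BPD the plan already deals with death, by combining the two. The durations face the same competing event without any such step.

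Readers will take these outcomes as evidence on respiratory morbidity and resource use. A shorter stay produced by deaths could be reported as a benefit.

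**Working it through.** **Plan figures.** The article gives no expected mortality, length of stay or standard deviation for the durations, so it has no figure of its own to reproduce on this point. Its sample size of 324 is for the primary outcome (45% v 30%) and reproduces: 163 per arm with pooled variance (326 in total), 162 per arm with the arcsine formula (324). It matters below only as 162 infants per arm.

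**Formula.** Let p be mortality in an arm, S the mean duration in survivors and D the mean duration in infants who die.

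- Arm mean = (1 − p) × S + p × D
- With the same S and D in both arms, the difference (arm B − arm A) = −(p_B − p_A) × (S − D)

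Survivors do equally well in both arms by construction, so any non-zero result comes from deaths alone.

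**Hospital stay, assumed S = 60 to 80 days and D = 7 days.**

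- 4 points more deaths: 0.04 × (53 to 73) = 2.1 to 2.9 days shorter
- 6 points more deaths: 0.06 × (53 to 73) = 3.2 to 4.4 days shorter
- Equal mortality: 0

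**Other assumed inputs, arm A mortality 5%.**

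| S, D (days) | Arm B 8% | Arm B 10% | Arm B 15% |
|---|---|---|---|
| 60, 5 | −1.65 (−2.9%) | −2.75 (−4.8%) | −5.5 (−9.6%) |
| 75, 7 | −2.04 (−2.8%) | −3.4 (−4.7%) | −6.8 (−9.5%) |
| 75, 15 | −1.8 (−2.5%) | −3.0 (−4.2%) | −6.0 (−8.3%) |

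For example, with S = 75 and D = 7, arm A has 0.95 × 75 + 0.05 × 7 = 71.6 days and arm B at 10% has 0.90 × 75 + 0.10 × 7 = 68.2 days, a difference of −3.4.

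**Non-invasive and total support.** The same formula applies. The shift favours the arm with more deaths whenever survivors accumulate more days than infants who die early (S > D). That is plausible, but the article gives no durations from which to size it.

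**Invasive ventilation.** Here S may be small. The plan expects the primary outcome at an "incidence of around 45% in the fentanyl group in our trial" and about 30% with saline, so 55% and 70% would not reach it within 24 h. Many infants may therefore total 0 days over the whole admission, although later ventilation would reduce that share. With mortality of 5% v 10%:

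- S = 6, D = 2: 5.8 v 5.6, difference −0.2 days
- S = 3, D = 7: 3.2 v 3.4, difference +0.2 days
- S = 3, D = 10: 3.35 v 3.7, difference +0.35 days

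The sign follows S − D and is not known in advance.

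**Size against precision.** If stay has a standard deviation of 25 to 30 days (assumed), the standard error of the mean difference is SD × √(2/162) = SD × 0.111, or 2.8 to 3.3 days. The 4-point shift of 2.1 to 2.9 days is about one standard error or less.

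**The case against.** The strongest reply is that the article names an effect measure and does not say that deaths enter at their raw duration. A mean difference could be taken among survivors, the intention-to-treat sentence concerns the primary analysis, and an analysis plan that is not shown may hold a rule. All of that is possible. But the point does not rest on a missing detail. It rests on two things the article states: totals open to the end of the admission, and a difference in means. Followed as written, they average admissions ended by death with admissions ended by recovery. Restricting to survivors would not repair the comparison either, because it conditions on an event after randomisation that treatment might affect.

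It is also true that death is reported separately and within the BPD composite, so a mortality difference would be visible elsewhere in the report. That helps a careful reader but leaves the duration estimates themselves hard to interpret.

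Three stronger readings are tempting and are not supported:

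- That all four durations flatter the arm with more deaths. For invasive ventilation the best score is 0, not a few days before death, and infants who die may be ventilated longer than the average survivor.
- That deaths would reverse the sign of a real effect. The calculation assumes no effect in survivors, so it shows a spurious difference and not a reversal.
- That the arms will differ in mortality by 4 to 6 points. The article gives no mortality figure, and these differences are illustrations.

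**Conclusion.** The concern holds for hospital stay and, provided survivors accumulate more support than infants who die early, for non-invasive and total respiratory support. With unequal mortality, the planned mean difference credits the arm with more early deaths. For stay, a 4-point difference is worth about 2 to 3 days if survivors stay 60 to 80 days and deaths fall around day 7. With equal mortality and equal timing of death it is worth nothing. All of these inputs are assumptions, so the size in this trial is unknown.

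For invasive ventilation, survival and duration are also mixed, but the distortion could go either way and is small on the inputs tried (−0.2 to +0.35 days).

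These are secondary outcomes. The primary outcome is outside this point. The change should be made, but the trial's main conclusion does not depend on it.

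**What to change.** Before unblinding, and preferably before the masked Group A v Group B results described under Blinding are produced, make the between-arm comparison on measures that do not reward death:

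- **Ventilation and support.** Days alive and free of invasive ventilation, and days alive and free of any respiratory support, up to 36 weeks PMA, with deaths scored 0. Compare by a rank-based method or a bootstrap mean difference. Stratify or adjust for the gestational-age stratum, because the window depends on gestational age at birth: 12 weeks (84 days) if born at 24 weeks, 7 weeks (49 days) if born at 29.
- **Hospital stay.** Time to discharge alive, with death as a competing event or ranked worst.
- **Listed raw durations.** Keep all four as descriptive results, shown for survivors and with deaths by arm beside them.

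The cost is mainly wording, since 36 weeks PMA and hospital discharge are already follow-up points. The new measures need dates of support and of death, and the Data collection section does not list these, so their availability should be confirmed. Days-free measures are less intuitive than raw durations, weight death by convention, and omit support after 36 weeks PMA. The descriptive durations cover that last gap.
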